**7.4 (a) Do the Subject Information Statement and Consent Form :**

|  | – | give the title of the project on every page? (Use a short title as appropirate | **No** | **Yes** |
| --- | --- | --- | --- | --- |

|  | – | are the page numbers expressed as page 1 of .., 2 of .., 3 of .. etc? | **No** | **Yes** |
| --- | --- | --- | --- | --- |

|  | – | include an assurance that participation is voluntary and subjects are permitted to withdraw from the project at any time without penalty or prejudice? | **No** | **Yes** |
| --- | --- | --- | --- | --- |

|  | – | include an assurance that participation is voluntary and subjects are permitted to withdraw from the project at any time without penalty or prejudice? | **No** | **Yes** |
| --- | --- | --- | --- | --- |

|  | – | give the name and telephone number of an appropriate investigator? | **No** | **Yes** |
| --- | --- | --- | --- | --- |

|  | – | give a telephone number for an Executive Officer of the IEC, should a subject wish to make a complaint about the conduct of the research project? | **No** | **Yes** |
| --- | --- | --- | --- | --- |

If you answered **NO** to any of the above, give reasons.

|  | **(b)** | **Are the first page of the Subject Information Statement and Consent Form printed on appropriate institutional letterhead?** | **No** | **Yes** |
| --- | --- | --- | --- | --- |

**SECTION 8: DESCRIPTION OF PROJECT**

**8.1 Describe the project in lay terms including the aims, hypotheses, potential significance and research plan (including inclusion/exclusion criteria, where relevant). You must satisfy the IEC that the study is valid and in accordance with accepted principles governing research involving humans. Where relevant, provide the projected number, sex and age range of subjects. The description must be no longer than 2 pages and must be in a font size of at least 10 points.**

The specific aims of this proposal are to:

1. Characterise the physiological, endocrine and anthropometric responses to short-term overfeeding (3d and 4wks) in lean and overweight subjects with and without a genetic predisposition for T2DM.
2. Characterise the physiological, endocrine and anthropometric responses to subsequent weight loss in overweight subjects.
3. Identify mechanisms dysregulating fatty acid oxidation and oxidative phosphorylation in skeletal muscle by measuring fat oxidation in muscle homogenates, as well as by gene expression, protein and enzymatic assays.

**Research Plan:**

**Subjects:**

| **FH-** | 20 lean to overweight subjects with no family history of T2DM |
| --- | --- |
| **FH+** | 20 lean to overweight subjects who have >1 first degree relative with T2DM |

Groups will be matched for sex and age.

Inclusion Criteria:

- Sedentary (<60 min formal exercise per week)
- Aged 20-65 years

Exclusion Criteria:

- Personal history of diabetes, cardiovascular disease, hypertension or eating disorder
- Recent weight change (larger than 3kg in the past 3 months)
- Smoking
- Regular use of medications, except oral contraceptives
- Individuals with alcoholism or other substance abuse
- Pregnancy or lactation, women who are planning to become pregnant or who are not using adequate measures of birth control.

**Screening Visit:** Participants will attend the CRF so that fasting blood samples can be collected (for measurement of glucose and insulin) and resting metabolic rate (RMR) will be determined. Subjects will give a 3-day diet history and will discuss their usual eating patterns with a study dietician. Subjects will then go to SVH for a DEXA scan. The total visit time will be 2-hours.

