**(d) Provide a brief lay description of the project (in less than 100 words).**

The prevalence of obesity is rapidly increasing in Australia is estimated to cost >$3.6 billion per year. In this study, we will investigate the effects of over-nutrition in lean individuals, overweight individuals and individuals who have a strong family history of diabetes. The aims is to distinguish physiological and endocrine characteristics of individuals who store more fat in response to overfeeding and identify defects in machinery involved in fat oxidation in skeletal muscle. We will re-examine overweight individuals again after 10% weight loss. This study will determine whether overweight and lean subjects behave similarly when faced with over-nutrition, establish quantifiable markers to distinguish those at risk of insulin resistance and identify new targets for intervention.

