**SECTION 5: RECRUITMENT OF SUBJECTS**

**5.1 (a) How many subjects will be recruited?**

**40**

1. **How will the subjects be recruited?**

Subjects will be recruited by advertisement in newspapers and on radio

| **5.2** | **(a)** | **Does recruitment involve a direct personal approach from the researchers to the potential subjects?** | **No** | **Yes** |
| --- | --- | --- | --- | --- |

|  |  | If you answered **YES**, is there any pressure from researchers or others that might influence the potential subject to enrol? | **No** | **Yes** |
| --- | --- | --- | --- | --- |

If you answered **YES**, explain.

|  | **(b)** | **Does recruitment involve the circulation/publication of an advertisement, circular, letter, etc?** | **No** | **Yes** |
| --- | --- | --- | --- | --- |

If you answered **YES**, provide a copy and indicate where and how often it will be published.

A copy of the advertisement is included. We plan to utilise the Health Section of the Sydney Morning Herald and will advertise on an as needed basis.

| **5.3** | **Will subjects receive any financial or other benefits as a result of participation?** | **No** | **Yes** |
| --- | --- | --- | --- |

If you answered **YES**, what is the amount/benefit and the justification for this ?

Subjects will receive an amount up to $400 to pay for taxis or other transport costs, childcare or other associated expenditures for attending the Garvan Institute. Subjects will also be provided with their meals for 3-days prior to each metabolic testing day to standardise macronutrient composition, which is necessary for successful completion of the project.

| **5.4** | **Is the research targeting any particular ethnic or community group?** | **No** | **Yes** |
| --- | --- | --- | --- |

If you answered **YES**, which group is being targeted?

|  | If you answered **YES**, has this been done in consultation with a representative of this group? | **No** | **Yes** |
| --- | --- | --- | --- |

If you have not consulted a representative of this group, give reasons.

If you have consulted a representative, who have you consulted and how do they represent this group?

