**Study Design:**

**
[figure not shown]
**

Bold arrows denote a long day CRF visit (4-5h) and small arrows indicate a short visit (1-2 h). Three days of meals will be provided to subjects at required energy amounts before each long visit testing day to standardise nutrient composition (eg -3 to +3). Between days +3 and 25 subjects will follow their usual diets but will be provided with high energy snacks, drinks and desserts. These snacks will increase energy intake by 1250kal/day, while minimizing feelings of fullness. Subjects will drink IsoSource 1.5Cal milkshakes plus BeneCal (500kcal) and will choose from lists of high energy foods that are ~250 kcals per serve (eg: chocolate bars, potato crisps, chocolate mousse). Subjects will be asked to record whether the total menu prescribed was consumed daily and will fill out 3-day diet diaries on two occasions during the study. During the overfeeding phase, participants will attend the CRF once per week to visit the dietician, track weight change and answer a brief activity questionnaire.

Lean participants will only be tested during the overfeeding phase of the study (d28). We expect lean subjects will return to their usual weight within 4-weeks, but they will be offered access to the dietician to assist this process if necessary. Overweight subjects will be placed on liquid calorie diets (800kcal/d, OptiFast, Novartis Nutrition) until 10% weight loss is achieved (6-8weeks). Any subjects not achieving 10% weight loss by 10weeks will be deemed non-compliant and withdrawn from the study. Subjects will return to the clinic for counselling, weight and activity level checks every 2 weeks. Subjects will also return to the clinic at 3-days following initiation of the LCD diet and after 10% weight loss for metabolic testing. Once 10% weight loss is achieved, subjects will be slowly re-fed to weight maintenance over 7-10 days and then be placed back on original meal plan (minus 15% of calories for weight maintenance) for 3-d before the final visit is conducted.

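### Family-history groups are matched on sex and age only, with no lean/overweight numbers set, so the family-history contrast is open to confounding by adiposity and the lean/overweight split is uncontrolled

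*Protocol*

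**What the plan says.** Section 8.1 of the Protocol, under Subjects, defines two groups by family history: FH-, "20 lean to overweight subjects with no family history of T2DM", and FH+, "20 lean to overweight subjects who have >1 first degree relative with T2DM". The control on comparability is one sentence: "Groups will be matched for sex and age". Section 5.1 gives the total as 40.

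Three other places treat weight class as part of the design:

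- Aim 1 (section 8.1) concerns responses to overfeeding "in lean and overweight subjects with and without a genetic predisposition for T2DM", which is a two-by-two layout.
- The lay description (section 1.1(d)) says: "This study will determine whether overweight and lean subjects behave similarly when faced with over-nutrition".
- Aim 2 concerns weight loss in overweight subjects alone. Study Design accordingly gives the two classes different paths: "Overweight subjects will be placed on liquid calorie diets", while lean subjects finish after overfeeding.

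The visible text gives no number or proportion of lean and overweight subjects, within or across the FH groups. The inclusion list has no BMI bounds. The one BMI range in the document, 25 to 30 kg/m2, is in section 2.2 in a remark about how long the diet may take.

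**The concern.** Family history is not randomised, so only matching or recruitment targets can protect the FH contrast by design. The rule protects it for sex and age and leaves adiposity out. If the FH+ group recruits more overweight people than the FH- group, a difference in response to overfeeding could reflect weight class rather than family history.

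The lean-versus-overweight comparison has less protection still. Matching operates between FH groups only, so lean and overweight subjects may differ in age (eligible range 20–65 years) and sex. The split between them is also open, and so is the number entering the weight-loss phase.

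Cell sizes are decided at recruitment. A later analysis plan can adjust for adiposity, but it cannot fill a thin cell or set the number available for Aim 2.

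**Working it through.** **Inputs from the Protocol.** 20 FH- and 20 FH+ (section 8.1); total 40 (section 5.1). The only figure that can be reproduced is 20 + 20 = 40, which agrees. The Protocol gives no effect size, SD, power or overweight prevalence, so everything below rests on stated assumptions.

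**1. Imbalance between FH groups.** Let X₁ and X₂ be the overweight counts in the two groups, independent Binomial(20, p) with the same p. The probability of a gap of at least k is the sum of P(X₁ = i)·P(X₂ = j) over |i − j| ≥ k.

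| Assumed overweight prevalence | Gap ≥ 4 of 20 | Gap ≥ 6 of 20 | Some cell has ≤ 5 subjects |
|---|---|---|---|
| 30% in both | 23% | 6% | 66% |
| 50% in both | 27% | 8% | 8% |
| 70% in both | 23% | 6% | 66% |

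If prevalence truly differed, say 40% against 60%, a gap of 6 or more would occur in about 32% of realisations. No section supports that particular pair; it shows only the direction.

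**2. Effect on an unadjusted FH contrast.** Shift = (gap / 20) × δ, where δ is the lean–overweight difference in the response, in within-cell SD units (assumed).

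- Gap 4: 4/20 × 0.5 = 0.10 SD; 4/20 × 1.0 = 0.20 SD.
- Gap 6: 6/20 × 0.5 = 0.15 SD; 6/20 × 1.0 = 0.30 SD.

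**3. Precision of lean versus overweight.** For a two-sample t-test (two-sided 5%, 80% power, 38 df), the detectable difference is proportional to √(1/n₁ + 1/n₂). It equals 0.91 SD at 20:20.

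| Lean:overweight, or the reverse | √(1/n₁ + 1/n₂) | Detectable difference (SD) | Power at 0.9 SD |
|---|---|---|---|
| 20:20 | 0.316 | 0.91 | 79% |
| 25:15 | 0.327 | 0.94 | 77% |
| 28:12 | 0.345 | 0.99 | 72% |
| 30:10 | 0.365 | 1.05 | 67% |
| 32:8 | 0.395 | 1.14 | 60% |

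**4. Number entering Aim 2.** The overweight total is Binomial(40, p). Its central 95% range is 14 to 26 at p = 50% and 7 to 18 at p = 30%.

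**5. With 10 per cell.** The overweight gap between FH groups is 0, weight class and family history are orthogonal, both main contrasts are 20 against 20, and 20 overweight subjects are recruited for Aim 2.

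**The case against.** Several counter-arguments have force.

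- *Imbalance is not certain.* A reader might infer that the contrasts **are** confounded, or picture an extreme split such as 14 lean and 6 overweight in one group and the reverse in the other. At equal 50% prevalence a gap that large (8 or more of 20) occurs in only 1.7% of realisations. The documents support a risk, not a fact.
- *The shift needs a difference in response.* Aim 1 is about responses to overfeeding. A lean–overweight difference in baseline level cancels in within-person change, so δ must be a difference in the change itself. The Protocol gives no value for it.
- *Adjustment is possible.* The Protocol names no test, so an inflated false-positive rate for an unadjusted t-test cannot be charged to it. DXA is taken at screening, and adjusting the FH contrast for weight class at a split such as 14/6 against 8/12 raises its variance by only about 10%. The choice of model belongs to the analysis plan and is not faulted here.
- *Drift in class during overfeeding.* Section 2.13 projects a gain of 3.8 kg, so a reader might infer that lean subjects near a cut-off would be reclassified by day 28. The text does not support this: it expects lean subjects to return to their baseline or usual weight, so they are called lean by their state before overfeeding.
- *Some restriction on weight exists.* The group definitions limit entry to lean through overweight people. What is missing is the cut-offs.
- *The source is short.* It is an ethics form with a two-page limit on this section, and the design figure is not shown. The figure might show a split; the text gives none.

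These points reduce the size and certainty of the problem. They do not supply the cell sizes, the number for Aim 2, or comparability of lean and overweight subjects on age and sex.

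**Conclusion.** The point stands as a weakness of the recruitment rule that should be fixed. Matching on sex and age alone, with no lean or overweight numbers, does not secure the comparisons that Aim 1 and the lay summary promise, and it leaves the size of Aim 2 to chance.

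The size is moderate. With equal prevalence, roughly one realisation in four has a gap of 4 or more of 20, worth 0.1–0.2 SD on an unadjusted FH contrast for δ of 0.5–1 SD. Analysis could remove most of that shift. It could not remove the loss of precision from an uneven split, which at 30:10 takes the detectable lean–overweight difference from 0.91 to 1.05 SD, nor the uncertainty about how many subjects inform Aim 2. The prevalences, δ and the independence of recruits are all assumptions. The absence of weight class from the matching rule and of any stated split in the visible text is not.

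**What to change.** Change the matching sentence in section 8.1 to: *Groups will be matched for sex, age and BMI class.* State the BMI bounds for lean and overweight in the inclusion criteria, with class assigned from baseline BMI before overfeeding. Add recruitment targets of about 10 lean and 10 overweight in each FH group. Equal targets are one reasonable choice; the essential change is that adiposity enters the matching and the planned numbers are written down.

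The change uses the same 40 participants and needs no new measurements, since weight, height and DXA are already planned. The cost is that the last cells may fill more slowly, particularly in FH+, where the family-history criterion already narrows the pool. It has to be made before enrolment, because recruited cells cannot be rebalanced afterwards without adding subjects.

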**Study Design:**

**
[figure not shown]
**

Bold arrows denote a long day CRF visit (4-5h) and small arrows indicate a short visit (1-2 h). Three days of meals will be provided to subjects at required energy amounts before each long visit testing day to standardise nutrient composition (eg -3 to +3). Between days +3 and 25 subjects will follow their usual diets but will be provided with high energy snacks, drinks and desserts. These snacks will increase energy intake by 1250kal/day, while minimizing feelings of fullness. Subjects will drink IsoSource 1.5Cal milkshakes plus BeneCal (500kcal) and will choose from lists of high energy foods that are ~250 kcals per serve (eg: chocolate bars, potato crisps, chocolate mousse). Subjects will be asked to record whether the total menu prescribed was consumed daily and will fill out 3-day diet diaries on two occasions during the study. During the overfeeding phase, participants will attend the CRF once per week to visit the dietician, track weight change and answer a brief activity questionnaire.

Lean participants will only be tested during the overfeeding phase of the study (d28). We expect lean subjects will return to their usual weight within 4-weeks, but they will be offered access to the dietician to assist this process if necessary. Overweight subjects will be placed on liquid calorie diets (800kcal/d, OptiFast, Novartis Nutrition) until 10% weight loss is achieved (6-8weeks). Any subjects not achieving 10% weight loss by 10weeks will be deemed non-compliant and withdrawn from the study. Subjects will return to the clinic for counselling, weight and activity level checks every 2 weeks. Subjects will also return to the clinic at 3-days following initiation of the LCD diet and after 10% weight loss for metabolic testing. Once 10% weight loss is achieved, subjects will be slowly re-fed to weight maintenance over 7-10 days and then be placed back on original meal plan (minus 15% of calories for weight maintenance) for 3-d before the final visit is conducted.

All metabolic tests will be conducted at the Garvan Clinical Research Unit following a 12h overnight fast. Briefly, **weight,** will be measured in a hospital gown after the participant has voided. **Height, blood pressure, waist and hip circumference** will be also measured as previously described (19). Insulin sensitivity will be measured by the gold standard, a **2-h** **hyperinsulinemic euglycaemic clamp** (60mU/m2/min). We will also measure **resting metabolic rate** for 30 minutes fasting and during the last 30-minutes of the clamp. Fastingserum samples will be collected and stored at –80C until study completion for measurement of glucoregulatory matabolites and hormones, lipidsand adipocytokines. A muscle and fat biopsy will be performed before the clamp. Following the clamp, lunch will be served. Body composition will be measured by **DXA** at screening, d28 and after weight loss.

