No, there is no direct benefit to the participant. However, subjects will be provided with information about their health (lipids, insulin, glucose levels). Overweight subjects will also be asked to lose 10% of their initial body weight which will probably reduce lipids and insulin concentration. The subjects will also gain knowledge on their individual energy requirements for weight maintenance and will have access to a dietician during the study.

| **2.12** | **Will the true purpose of the research be concealed from the subject(s)?** |  |  |  |
| --- | --- | --- | --- | --- |
|  | **No** | **Yes** |  |

If you answered **YES**, provide details of the concealment and any debriefing.

| **2.13** | **Will the research induce any psychological or physical stress in the subject?** |  |  |  |
| --- | --- | --- | --- | --- |
|  | **No** | **Yes** |  |

If you answered **YES**, state what form this stress will take.

The use of cannulae for venous sampling and the clamp study may cause some persons with fear of needles undue stress. We will only include subjects who are comfortable with the procedures as outlined and all will be offered local anaesthetics to minimise possible distress. Subjects who are claustrophobic will be excluded from the study as the placement of the ventilated hood may cause undue stress. Subjects will be also asked to over-eat by 5225kJ/day (1250kcal/day) over their usual weight maintenance requirements. From calculations based on animal data this level of over-consumption will result in 3.8kg of weight gain. We expect that lean individuals will return to baseline weight within 4-weeks. If this process takes longer than 4-weeks, subjects will be provided with additional counselling and access to the study dietician. As part of the study, the overweight group will reduce weight by 10% by liquid calorie diet that is provided by Garvan.

| **2.14** | **Could participation in the research adversely affect the subject(s)?** |  |  |  |
| --- | --- | --- | --- | --- |
|  | **No** | **Yes** |  |

If you answered **YES**, what facilities/trained personnel are available to deal with such problems?

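### For 22 of the 28 overfeeding days each person's energy surplus rests on self-report, so fat stored by day 28 is confounded with the surplus actually eaten

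*Protocol*

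**What the plan says.** The lay description (Protocol 1.1(d)) gives an individual-level purpose: to "distinguish physiological and endocrine characteristics of individuals who store more fat in response to overfeeding". The first specific aim in section 8.1 covers responses to "short-term overfeeding (3d and 4wks) in lean and overweight subjects".

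The Study Design text in section 8.1 controls meals only around the long test visits: "Three days of meals will be provided to subjects at required energy amounts before each long visit testing day to standardise nutrient composition". For the rest of the overfeeding period, "Between days +3 and 25 subjects will follow their usual diets but will be provided with high energy snacks, drinks and desserts". It then states the effect as a fact: "These snacks will increase energy intake by 1250kal/day". Question 2.13 describes the same surplus against another baseline: "Subjects will be also asked to over-eat by 5225kJ/day (1250kcal/day) over their usual weight maintenance requirements".

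Intake monitoring is given in one sentence: "Subjects will be asked to record whether the total menu prescribed was consumed daily and will fill out 3-day diet diaries on two occasions". The diaries are placed only somewhere within the study. Participants also attend weekly during overfeeding to see the dietician, be weighed and complete a short activity questionnaire. Body composition is measured by DXA at screening, at day 28 and after weight loss. Resting metabolic rate is measured fasting and late in the clamp.

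**The concern.** Energy stored over four weeks is the surplus eaten multiplied by the fraction of it retained. To describe people as storing more fat in response to overfeeding, the surplus must be either equal across people or known for each of them. Between days 3 and 25 neither is secured.

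The daily record, as worded, captures whether the whole prescribed menu was eaten. The text does not ask for a quantity when it was not. Nor does it say whether the prescribed menu includes the home diet. If it covers only the supplements, someone who ate all of them but took smaller meals would still record full compliance.

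At stake is interpretation. Hormonal or muscle features that go with greater fat gain could be read as features of efficient storage when they partly follow from having eaten more.

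**Working it through.** **Inputs from the protocol.** Overfeeding lasts 4 weeks, with testing at day 28. The self-selected window runs from day 3 to day 25. The target surplus is 1250 kcal/day (5225 kJ/day). The supplements are a 500 kcal drink plus serves of about 250 kcal. The expected weight gain is 3.8 kg (question 2.13, attributed there to animal data). There are two 3-day diaries.

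**The plan's own figures.**
- 1250 × 4.18 = 5225 kJ, which agrees.
- 500 + 3 × 250 = 1250 kcal, which agrees.
- Total target surplus: 28 × 1250 = 35,000 kcal.
- The 3.8 kg implies 35,000 / 3.8 = 9,211 kcal per kg gained, if it refers to 28 days with all the surplus stored. The protocol gives no energy density. Assumed densities of 7,000, 7,700 and 9,400 kcal/kg would give 5.0, 4.5 and 3.7 kg. The figure can be neither confirmed nor refuted, and is used below only as a scale.

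**Share of the surplus that is not controlled.**
- Days on self-selected diet: 25 − 3 = 22, and 22 / 28 = 79%.
- Days on provided meals: 28 − 22 = 6. This infers that days 25 to 28 are the three days before the day 28 visit.
- Surplus falling in that window: 22 × 1250 = 27,500 of 35,000 kcal.
- Best possible diary coverage: 6 / 22 = 27%, and only if both diaries fall inside the window.

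**What a difference in compensation does.** Take two people with identical storage, one of whom cuts the usual diet by an assumed amount for 22 days. The difference in gain is 22 × offset / 9,211.

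| Assumed offset (kcal/day) | Surplus lost (kcal) | Share of 35,000 | Difference in gain |
|---|---|---|---|
| 100 | 2,200 | 6% | 0.24 kg |
| 250 | 5,500 | 16% | 0.60 kg |
| 500 | 11,000 | 31% | 1.19 kg |

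An offset shared equally by everyone would lower all gains and would not by itself reorder people. Only the spread between people matters.

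**How much of the variation could be surplus eaten.** Let *a* = 22 × SD / 35,000 be the coefficient of variation (CV) of surplus, where SD is the between-person SD of the daily offset, and let *c* be the CV of true storage efficiency. If the two are independent, the share of variance in stored energy due to surplus is about *a*² / (*a*² + *c*²). All SDs and CVs here are assumed.
- SD 200 kcal/day: *a* = 0.126. With *c* = 0.20 the share is 28%.
- SD 400 kcal/day: *a* = 0.251. With *c* = 0.20 the share is 61%.
- With *c* from 0.10 to 0.30 and SD from 200 to 400, the share runs from 15% to 86%.

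**What the diaries could recover.** Assume a day-to-day intake SD within a person of 300, 500 or 700 kcal, accurate reporting, and six representative days. The standard error of the 22-day mean is SD / √6 × √(1 − 6/22), which is 104, 174 or 244 kcal/day. That is before any error in the screening diet history.

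**The case against.** The best defence is that the monitoring is more than a tick-box. Besides the daily record there are two diet diaries, and weekly dietician visits with weighing would flag someone who is plainly not overeating. DXA at screening and day 28 measures the tissue gained and splits it into fat and lean, so fat gain can be set against total weight gain and resting metabolic rate. This stands, and it rules out a stronger reading that a reader might infer: that efficient storers cannot be told apart at all from people who ate more. The separation is weak and open to confounding, not impossible. But weight and DXA measure what was stored, not what was eaten. They do not supply the missing denominator.

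Two further inferences are not supported. A reader might suppose that the analysis will credit everyone with 1250 kcal/day; the protocol states this as the prescribed or expected surplus and nowhere fixes it as an analysis input. A reader might also suppose that the comparison by family history, or of lean with overweight participants, is biased. That needs adherence or compensation to differ by group, and the document gives no evidence that it does.

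It is also fair to say that the schedule figure is not shown and may give the diary timing, that the record form is not shown, and that storing more fat is the wording of the lay description, while the specific aims speak more generally of responses to overfeeding. These points limit the weight of the concern. They do not remove it, because the first aim includes the 4-week response and the text describes no measure of total expenditure.

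Finally, counting serves cannot detect smaller home meals, and self-report may err differently in lean and overweight people. This is a good reason not to make fat gain per unit of reported surplus the main outcome.

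**Conclusion.** The concern holds as one of confounding. For 79% of the overfeeding period, individual surplus is known only through self-report and at most six diary days. Differences in fat stored at day 28 therefore mix storage with intake, which weakens the aim of distinguishing people who store more fat.

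The size depends on assumptions. A difference of 250 to 500 kcal/day in compensation between two people corresponds to 0.6 to 1.2 kg on the scale implied by the protocol's 3.8 kg. The share of variance due to intake could be small or dominant (15% to 86%), depending on spreads that the protocol does not give.

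The 3-day response, obtained on provided meals, is not affected. The matter belongs in the protocol because no later analysis can recover intake that was not recorded.

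Separately, question 2.13 sets the surplus over weight-maintenance requirements, while Study Design adds the snacks to the usual diet. These baselines coincide only for someone whose usual diet happens to meet maintenance needs, so even the nominal surplus is not uniquely defined.

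**What to change.** In the Study Design text of section 8.1:

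1. Have participants record each day the number of shakes and of roughly 250 kcal serves actually consumed, in place of a record of whether the whole menu was eaten.
2. Place both 3-day diaries within days 3 to 25, one early and one late, so that they can be compared with the 3-day diet history taken at screening. If the schedule figure already does this, say so in the text.
3. Report unadjusted fat gain as the main result. Relate it to the estimated achieved surplus (supplements eaten plus change in background intake) only as a supportive sensitivity analysis.
4. Reconcile question 2.13 with Study Design, so that the surplus is defined against a single baseline. Which one is for the investigators to decide.

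The cost is a redesigned daily form, fixed diary dates and slightly more recording by participants, with no added visits or procedures. The limitation is that intake remains self-reported, so the adjustment will be partial.
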